**Methods:**

This study is an 8-week, parallel-design, open-label, three-arm, single-center randomized controlled trial. Eligible participants were pregnant women between 24 and 28 weeks of gestation, and they were diagnosed with GDM through an oral glucose tolerance test (OGTT). The participants in the three groups will receive nutrition education alone, nutrition education plus XOS inulin (XOS 2 g and inulin 10 g) 12 g/day, or nutrition education plus XOS inulin 24 g/day. Measurements will be taken at baseline, week 4, and week 8. The primary outcome will be the change in glycosylated serum protein (GSP), and the key secondary outcomes include changes in fasting glucose, fasting insulin (FINS), 2-h postprandial plasma glucose (2 h-PPG), HbA1c, total cholesterol (TC), triglycerides (TG), LDL cholesterol (LDL-C), HDL cholesterol (HDL-C), and changes in the gut microbiota.

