### Explanation for the choice of comparators {6b}

To determine whether a dose–response relationship exists between the dose of XOS inulin and blood glucose metabolism, two supplement doses, 12 g/day and 24 g/day, will be used in the two experimental groups.

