### Objectives {7}

We hypothesize that daily XOS-inulin supplementation improves glycolipid metabolism in GDM patients via modulation of gut microbiota. We designed this trial to test the efficacy of daily XOS inulin supplementation after the diagnosis of GDM for improving glycolipid control and changing the gut microbiome compared with standard dietary education. We also want to study the effects of XOS inulin supplementation on pregnancy outcomes.

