### Statistical analysis {20a}

Statistical analyses will be performed using the R 4.3.0 software. The Shapiro–Wilk test will be used to check for a normal distribution of the data. Continuous variables with a normal distribution will be presented as the mean (standard deviation [SD]); non-normal variables will be reported as the median (interquartile range [IQR]). Categorical data will be compared among the three groups using chi-square tests and partitions of the chi-square method. Linear models will be used to compare the mean values of the outcome variables among the three groups, adjusting for baseline values (e.g., age, BMI, nationality, gestational weeks, calorific intake). GSP Changes from baseline to week 8 will be analyzed using mixed-effects models with treatment group, time, and group × time interaction as fixed effects, adjusting for baseline GSP. *P*-value of less than 0.05 will be considered statistical significance. Post hoc pairwise comparisons were adjusted using the Bonferroni method to reduce the probability of type I error.

We will evaluate gut microbial diversity through complementary alpha- and beta-diversity analyses. For alpha diversity (within-sample microbial complexity), we will calculate three complementary metrics: Chao1 index (quantifying species richness), Shannon index (reflecting both richness and evenness), and Simpson index (measuring dominance of abundant species). Alpha-diversity differences between groups will be assessed using the Wilcoxon test. The cross-sectional difference in beta diversity (between-sample compositional differences) between the groups will be assessed by permutational analysis of variance (PERMANOVA) of Bray–Curtis dissimilarity and illustrated by PCoA models [35]. The significant bacterial taxa responsible for discrimination between the three groups will be identified via linear discriminant analysis (LEfSe) with linear discriminant analysis (LDA) [36]. Some multiple comparisons, such as differential abundance analysis of the microbiota, will be corrected using the Benjamini–Hochberg false discovery rate (FDR).

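### Significant taxa are to be called by a three-group LEfSe rule with no named arm contrast, so its output does not directly give the comparison with dietary education that the trial aims to make

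*Protocol article*

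**What the plan says.** The abstract (Methods) sets out three arms: "nutrition education alone, nutrition education plus XOS inulin (XOS 2 g and inulin 10 g) 12 g/day, or nutrition education plus XOS inulin 24 g/day". It lists among the key secondary outcomes "and changes in the gut microbiota". Objectives {7} states the microbiome aim as "changing the gut microbiome compared with standard dietary education".

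Statistical analysis {20a} then gives the rule for naming taxa: "The significant bacterial taxa responsible for discrimination between the three groups will be identified via linear discriminant analysis (LEfSe". Multiplicity is covered by "Some multiple comparisons, such as differential abundance analysis of the microbiota, will be corrected using the Benjamini–Hochberg false discovery rate (FDR". The only sentence on pairwise comparisons (Bonferroni) closes the paragraph on clinical outcomes, before any microbiome text, and is not linked to taxa. For taxa the article gives no reference arm, no arm contrast and no LEfSe multi-class setting.

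**The concern.** The aim calls for two comparisons with one reference arm: 12 g versus education and 24 g versus education. The stated rule asks whether a taxon differs anywhere among three groups and then names one of them. Two of the three groups receive different amounts of the same product, so a taxon that both doses move is still listed under a single arm.

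At stake is what a reader takes from the list of taxa. An entry under the 24 g arm invites the conclusion that 24 g does something that 12 g does not. An entry under the 12 g arm invites the reverse. The rule tests neither statement. The taxon may truly change while the arm named beside it is uninformative.

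**Working it through.** The plan gives no figure on this point, so there is none to reproduce. The check has three parts.

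**1. What is asked and what is delivered.** Write E, L and H for education, 12 g and 24 g, and m for a taxon's mean abundance.

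- Needed for the aim: L versus E and H versus E. A statement about dose also needs H versus L.
- Delivered by three-class LEfSe: a Kruskal–Wallis screen of the hypothesis that E, L and H have the same distribution, an LDA score, and label = the arm with the largest of m(E), m(L), m(H). Pairwise rank tests may act as an internal filter, but they are not reported as estimates or adjusted p-values for a named contrast.
- Benjamini–Hochberg adjusts p-values. It does not determine which arms are compared.

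**2. Symmetry.** If both doses raise a taxon equally, L and H are interchangeable. Any screen that treats the arms alike then leaves each with the same chance of having the larger mean, so the label splits 50/50. This needs no assumption about effect size or SD. Likewise, if only H falls, E and L are interchangeable and share the label, and H is almost never named.

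**3. Illustrative simulation.** Inputs:

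- From Sample size {14}: 37 per arm (before the dropout allowance) and 45 per arm (randomised).
- From {20a}: significance level 0.05.
- Assumed, because the article gives none: log-normal abundance, log-SD 1, true shift of 0.8 SD on the log scale.
- 4000 runs per scenario; Kruskal–Wallis at unadjusted 0.05; label to the arm with the highest mean.

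Results at n = 37 / n = 45; label shares are among flagged runs:

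| True effect | Flagged | Label education | Label 12 g | Label 24 g |
|---|---|---|---|---|
| Both doses raise equally | 93.9% / 97.3% | 0.1% / 0.0% | 49.7% / 50.0% | 50.3% / 50.0% |
| Only 24 g raises | 94.1% / 97.3% | 0.3% / 0.1% | 0.3% / 0.1% | 99.4% / 99.8% |
| Both doses lower equally | 93.6% / 97.2% | 99.6% / 99.6% | 0.2% / 0.2% | 0.2% / 0.2% |
| Only 24 g lowers | 94.1% / 97.4% | 48.5% / 50.0% | 51.4% / 50.0% | 0.1% / 0.0% |
| Only 12 g lowers | 94.4% / 97.4% | 49.6% / 50.0% | 0.0% / 0.0% | 50.4% / 50.0% |

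Read down the last column: a 24 g label is what one gets when only 24 g raises the taxon, in half the runs when both doses raise it equally, and in half when only 12 g lowers it. An education label is equally ambiguous about which dose lowered the taxon.

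Effect of the multi-class setting when both doses raise equally:

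- Wilcoxon step added, at least one arm must differ from both others: flagged 86.2% / 92.6%; 24 g label in 50.6% / 50.1% of these.
- Wilcoxon step added, all three pairs must differ: flagged 3.0% / 4.1%. The false dose label becomes rare, but nearly all such true effects are missed.

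The effects need not be exactly equal. A separate simulation assumed 40 per arm, a 1.7-fold rise at 12 g, a 2-fold rise at 24 g and log-SD 0.8 to 1.2. The lower dose got the label in 19% to 26% of flagged runs.

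For comparison, with equally effective doses an explicit 24 g versus 12 g test at unadjusted 0.05 is significant for about 5% of taxa, by definition of the level. Under the first two settings, every flagged taxon carries a single-arm label.

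**The case against.** The best defence is that the article does not call LEfSe the only taxon analysis. The Benjamini–Hochberg sentence mentions differential abundance analysis and could cover a companion set of arm comparisons. The Wilcoxon test named for alpha diversity is a two-sample test, so comparisons between pairs of arms are contemplated. Data management {19} refers to a statistical analysis plan, which is not shown, and LEfSe settings, thresholds and follow-up tests commonly belong there. The Discussion describes the work on microbiota and metabolic outcomes as preliminary.

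Much of this stands. Added pairwise tests are not excluded, and the absence of a multi-class setting is no fault in an article. The flag rates above omit Benjamini–Hochberg and the LDA threshold, so they are probably too high. But the article does not merely leave a gap: it states the rule by which taxa become significant, and that rule is not the comparison in Objectives {7}. Benjamini–Hochberg lowers how often a taxon is flagged. It does not change the 50/50 split among flagged taxa.

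Two stronger readings are tempting and are not supported:

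- A reader might infer that the trial promises a dose-response result for taxa. Section {6b} states that purpose as "To determine whether a dose–response relationship exists between the dose of XOS inulin and blood glucose metabolism", which concerns glucose and not bacteria.
- A reader might infer that LEfSe can never show which dose differs from education. When only one dose raises a taxon, the label is right: for 24 g, in over 99% of flagged runs.

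**Conclusion.** The point holds in a limited form. The stated rule for significant taxa does not directly answer the comparison with education, and its arm label is unreliable in two situations: both doses raise a taxon by similar amounts, or only one dose lowers it. The roughly even split in those cases rests on symmetry alone. All frequencies of flagging, and the 19% to 26% figure, rest on assumed distributions and effects and on a LEfSe setting that the article does not state. They illustrate the mechanism and do not predict this trial's error rate. The matter concerns interpretation of a key secondary, mechanistic outcome. The primary GSP analysis is untouched. The change is worth making because it is cheap, not because the trial's main conclusion depends on it.

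**What to change.** Replace the LEfSe sentence as the rule for calling taxa:

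- Estimate week 8 contrasts of 12 g versus education and 24 g versus education for each taxon, with 24 g versus 12 g as a separate contrast.
- Adjust each for the taxon's week 0 abundance, since the outcome is change and stool is collected at week 0 as well as week 8.
- Use a suitable differential-abundance model, for example one on log-ratio abundance.
- Apply Benjamini–Hochberg across taxa and contrasts, and call a taxon only from these adjusted results.
- Keep LEfSe and LDA scores as an illustrative ranking, and state that no arm-specific or dose claim will be drawn from the label.

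The cost is a change of analysis wording and a little more work in R, with no new samples, visits or participants. The downside is that fewer taxa may be called than on a LEfSe list.

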## Methods for additional analyses (e.g., subgroup analyses) {20b}

No subgroup analyses are planned.

### Methods in analysis to handle protocol non‑adherence and any statistical methods to handle missing data {20c}

The analysis will follow an ITT approach, which will include the data from the excluded patients in the results. Missing data will be addressed by multiple imputations. Sensitivity analyses will examine per-protocol completers.

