### Criteria for discontinuing or modifying allocated interventions {11b}

Participants can withdraw from the trial or modify allocated interventions at any time for any reason. The investigator may discontinue patients from the trial to protect their safety or if they are unable or unwilling to continue with the trial (such as pregnancy occurs during trial participation). If adverse event is reported, doctors will also assess the patient to determine whether they should be withdrawn from the study or modify allocated interventions. The reason for each patient’s withdrawal, especially the occurrence of any adverse events, will be explained in detail.

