### Strategies to improve adherence {11c}

Participants must return all the product containers every month to assess compliance and actual soluble dietary fiber intake. Adherence to the assigned treatments will be assessed through the use of a daily calendar during each phone call and by counting the returned packs at the end of the trial. Compliance rate will be calculated using the following formula: compliance rate = (packs taken/packs prescribed) × 100. A compliance rate below 80% will be classified as poor compliance.

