### Outcomes {12}

The primary outcome measure will be the Change in GSP after 8 weeks of treatment across the different groups. GSP is a sensitive indicator of blood glucose levels in the last 3 weeks, making it particularly useful for monitoring pregnant women with diabetes. According to Morris et al., GSP levels correlate strongly with short-term glycemic control (fasting glucose: *r* = 0.798; postprandial: *r* = 0.846) and are measured via affinity chromatography targeting glycated serum proteins. This method allows frequent assessment of diabetic control, addressing the need for rapid treatment adjustments during pregnancy [20]. Secondary outcomes include fasting plasma glucose, 2 h-PPG, FINS, HbA1c, TC, LDL-C, HDL-C, TG, Wexner constipation score (WCS), the Bristol Stool Form Scale (BSFS), pregnancy outcomes, and changes in gut microbiota. Fasting venous blood will be collected at baseline (week 0), week 4, and trial completion (week 8). Blood samples will be processed within 2 h of collection (30-min room-temperature clotting, centrifugation at 3000 × g for 15 min), with serum/plasma aliquots stored at −80 °C. The Clinical Laboratory Department of Qingdao Municipal Hospital will test all the above laboratory indicators.

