### Adverse events {22}

Adverse events to be monitored include the following: Persistent diarrhea (defined as ≥ 3 loose stools per day for > 2 consecutive days); severe abdominal pain or bloating unresponsive to dose modification; clinically significant constipation (Wexner score ≥ 15 persisting after dietary intervention); confirmed hypersensitivity reactions (including but not limited to rash, angioedema, or dyspnea) attributable to XOS/inulin supplementation; hyperglycemia meeting diagnostic criteria (fasting plasma glucose > 7.0 mmol/L or 2-h postprandial glucose > 11.1 mmol/L on two consecutive measurements); new requirement for insulin therapy initiation; development of obstetric complications (preeclampsia, placental abruption, or other pregnancy-related emergencies); and hospitalization-requiring hyperemesis gravidarum or severe ketosis. Any adverse events should be reported to the researchers immediately. Investigators will also ask participants if they have any discomfort. All adverse events will be recorded in the participant case report forms. Once an adverse event is reported, doctors will assess the patient to determine whether they should be withdrawn from the study. All serious adverse events will be followed until resolution.

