## Discussion

This paper describes the methodology of a clinical trial to assess the effectiveness of inulin and XOS in treating GDM patients. This trial will build on the relationship between inulin and XOS supplementation and blood glucose levels in GDM patients. Although current dietary strategies have result in positive outcomes for GDM patients, 10%–30% of patients still have to undergo medical treatment, such as insulin therapy [37, 38]. If a daily inulin and XOS intake favorably alters GDM glycemic control, fewer mothers will depend on insulin. As a strong predictor of the development of chronic noncommunicable diseases in the future, effective control of GDM will ease pressure on the health care system.

In this study, we will investigate potential correlations between microbiota changes and metabolic outcomes in GDM patients. Studies revealed that GDM patients exhibit significantly lower microbial gene counts and Shannon indices compared to healthy pregnant women [39–41]. A reduction in the SCFA-producing species *Bifidobacterium bifidum* and *Lactobacillus casei* has been reported in GDM patients [40]. XOS, an emerging prebiotic [42], was reported to result in a significant increase in the genus *Bifidobacterium* in in vitro fermentation and clinical trials [43, 44]. Although one study concluded that prediabetic individuals had significantly lower blood sugar levels after 8 weeks of XOS intake [45], its effects on GDM remain unclear. As a type of dietary fiber, inulin is fermented in the digestive tract, resulting in the formation of short-chain fatty acids (SCFAs) which lowers serum glucose and lipid levels [46, 47]. However, the results concerning the impact of inulin on glucose levels in individuals with type 2 diabetes are inconsistent [48, 49], and the evidence concerning the effects of daily inulin supplementation on pregnant women with GDM is insufficient. Our research will evaluate the therapeutic potential of combined XOS and inulin supplementation in GDM patients and explore potential associations between gut microbiota modulation and metabolic outcomes preliminarily through intestinal flora analysis.

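### Withdrawal after hyperglycaemia or insulin start may leave week-8 GSP missing for outcome-related reasons, and the per-protocol completer analysis cannot test the imputation that fills the gap

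*Protocol article*

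**What the plan says.** Outcomes {12} defines the endpoint: "The primary outcome measure will be the Change in GSP after 8 weeks of treatment across the different groups". Data collection plan {18a} schedules GSP at weeks 0, 4 and 8.

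Adverse events {22} includes two events that are themselves poor glycaemic results: "hyperglycemia meeting diagnostic criteria (fasting plasma glucose > 7.0 mmol/L or 2-h postprandial glucose > 11.1 mmol/L on two consecutive measurements") and "new requirement for insulin therapy initiation". The consequence is a case-by-case decision: "Once an adverse event is reported, doctors will assess the patient to determine whether they should be withdrawn from the study". Criteria for discontinuing or modifying allocated interventions {11b} puts it slightly more broadly: "doctors will also assess the patient to determine whether they should be withdrawn from the study or modify allocated interventions". Trial design {8} makes the trial open-label, so these decisions are taken with the arm known.

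Section {20c} commits to intention-to-treat and says that the data of excluded women stay in the results. It then continues: "Missing data will be addressed by multiple imputations. Sensitivity analyses will examine per-protocol completers". No other sensitivity analysis is named. Statistical analysis {20a} gives a mixed-effects model for GSP with group, time, their interaction and baseline GSP. It has no term or rule for insulin.

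The Discussion says that "10%–30% of patients still have to undergo medical treatment, such as insulin therapy", and hopes that the supplement will reduce this.

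**The concern.** GSP is a marker of recent glycaemia. A woman taken out of the study for hyperglycaemia or for starting insulin would probably have had a high week-8 GSP without insulin. If no further blood is taken, her value is missing for a reason tied to the value itself. The loss would be unequal by arm if the fibre works, as the authors hypothesise, or if doctors who know the arm decide differently.

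Standard multiple imputation predicts her value from women who stayed and had similar earlier readings. That is adequate only if, given those readings, dropping out says nothing more about week-8 GSP. A sensitivity analysis should test this assumption. Restricting to per-protocol completers removes these women altogether, so it carries the same weakness, and agreement between the two analyses would reassure falsely.

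**Working it through.** **The plan's own figures.** No figure is given for withdrawals of this kind, so there is none to reproduce. The sample-size section supplies a scale, although it concerns HbA1c and not GSP.

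**Inputs from the article.** 45 women per arm; 37 (taken as per group) for 90% power at alpha 0.05; HbA1c difference 0.27%; 10–30% needing medical treatment.

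**Step 1, how many women.** 45 × 0.10 = 4.5 and 45 × 0.30 = 13.5 per arm. This is a ceiling: the 10–30% is a general range without a time window or split by arm, and withdrawal is not automatic.

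**Step 2, an effect size for illustration.** No SD is given. Solving n = 2·SD²·(1.960 + 1.282)²/Δ² for SD (two-sided) gives 0.27 × √(37/2) / 3.242 = 0.358. The implied effect is 0.27/0.358 ≈ 0.75 SD.

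**Step 3, simulation.** Two arms of 45, 2,000 runs, values in SD units. Assumptions:
- Correlations are 0.6 (weeks 0 and 4), 0.5 (weeks 0 and 8) and 0.65 (weeks 4 and 8).
- The week-4 effect is 60% of the week-8 effect.
- Failure occurs when a mixture of week-8 GSP and noise passes a threshold set to give 10%, 20% or 30% failures in controls. The weight on GSP (the link) is 0.6 or 0.9.
- Every failure loses week-8 GSP but keeps week 4.
- Imputation is represented by its point estimate: regression on arm, baseline and week 4.

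With no true effect, failures were equal by arm and every estimate lay within 0.006 SD of zero.

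With a true effect of 0.75 SD:

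| Failures, control / fibre | Link | Full data | Imputed | Completers |
|---|---|---|---|---|
| 10% / 4% | 0.6 | 0.752 | 0.718 | 0.708 |
| 10% / 2% | 0.9 | 0.757 | 0.683 | 0.660 |
| 20% / 10% | 0.6 | 0.745 | 0.688 | 0.670 |
| 20% / 6% | 0.9 | 0.752 | 0.629 | 0.595 |
| 30% / 16% | 0.6 | 0.752 | 0.678 | 0.655 |
| 30% / 12% | 0.9 | 0.751 | 0.586 | 0.544 |

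**Step 4, does the completer analysis reveal the problem?** The imputed estimate falls short of full data by 0.752 − 0.718 = 0.034 SD in the first row and 0.751 − 0.586 = 0.165 SD in the last. The gap between imputed and completer estimates is only 0.718 − 0.708 = 0.010 SD and 0.586 − 0.544 = 0.042 SD. In every row the completer estimate lies further from the full-data value than the imputed one. The check therefore shows a small gap and points the wrong way.

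**The case against.** The strongest reply is that intention-to-treat already covers this. Section {20c} keeps excluded women's data, so in the primary analysis they remain with baseline, any week-4 value and an imputed week-8 value. This stands: a reader might infer that failures drop out of every analysis, and that is not so. They leave only the completer analysis. They are also visible elsewhere, because adverse events go into the case report forms and withdrawal reasons are to be explained. But keeping data already collected does not supply a week-8 value that was never measured.

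Second, withdrawal is discretionary, and {11b} allows the intervention to be modified instead. Uneven loss by arm is therefore a possibility, not something that the article states. This also stands.

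Third, imputation models and tipping-point analyses commonly sit in a statistical analysis plan, which is not shown. Their absence is not the point here. The article itself names the sensitivity analysis, and the one it names does not examine the assumption that matters.

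Three stronger readings are tempting but unsupported:
- **Bias of either sign.** This would need withdrawal decisions to differ by arm in a particular way, which the documents do not show. The simulated bias was toward no difference.
- **Adherence selection in the fibre arms only.** Strategies to improve adherence {11c} says "A compliance rate below 80% will be classified as poor compliance", but nothing says that this threshold defines the per-protocol set.
- **A stated loss of power from insulin-lowered GSP.** That concerns women who stay and are measured on insulin, not women lost. Comparing arms with insulin effects included is also a legitimate choice.

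**Conclusion.** The concern holds in limited form. As written, week-8 GSP may be missing because of poor glycaemia, and neither standard imputation nor the completer analysis addresses this. If the fibre works, both would tend to understate its effect. In the scenarios above the shortfall is 0.03 to 0.17 SD for imputation (about 5% to 22% of the full-data effect) and 0.04 to 0.21 SD for completers (about 6% to 28%).

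These sizes rest on assumed correlations, an assumed 0.75 SD effect borrowed from HbA1c, and every failure losing its week-8 value. If fewer women are withdrawn, the bias is smaller. With no true effect and equal decisions by arm, it does not arise. This is a cheap improvement to a stated method, not a flaw that invalidates the design. It is best made before follow-up ends, because blood not taken at week 8 cannot be recovered at analysis.

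**What to change.** Leave all clinical decisions as they are, and change data collection and analysis only.

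1. In {11b}, {22} and {20c}, state that stopping the supplement or starting insulin does not end data collection. The scheduled week-4 and week-8 GSP are still taken unless the woman refuses, and are analysed in her randomised arm.
2. In {20c}, make delta-adjusted (tipping-point) imputation the sensitivity analysis for missing GSP: worsen the imputed values in steps, by arm, and report how far they must move before the conclusion changes. Keep per-protocol completers as supplementary only.
3. Add one sensitivity analysis that treats GSP after insulin start as unfavourable.
4. Report insulin start by arm from the adverse-event data already recorded.

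The cost is a few sentences and a little more analysis; the visits and blood tests are already scheduled. The one real downside is that the primary estimate will include any effect of insulin on GSP, which is why item 3 accompanies item 1.
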